**Nested study:**

**BACKGROUND:** High-quality primary care-based research requires adequate response rates. A recent systematic review identified some promising strategies including monetary incentives. However, most evaluations to date have focused on mail and telephone-based patient experience surveys.

**AIM:** assess the effect of different survey advertising methods using fact sheets embedded in consultation software (BetterConsult provided by the company HealthShare), on recruitment rate.

**DESIGN:** ABACAD replicated time series design where “A” are control periods and “B” and “C” are different behaviourally informed advertising strategies.

**PARTICIPANTS:** Patients who have recently seen their GP for back pain and have received back pain fact sheet. Participants could receive a fact sheet via one of two methods. The first method is directly from their GP who prints and/or emails the sheet to their patient. The GP determines which sheet they will provide and so receipt of the JAMA or ACHSQ fact sheet is non-random. The second method is patient-led access to a back pain fact sheet via an SMS system called BetterConsult. BetterConsult invites a patient to receive a back pain fact sheet after they see their GP. Whether the patient receives the JAMA or ACHSQ fact sheet is determined randomly by the fact sheet distributor, HealthShare. Patients can view the sheet on their smartphone or print the sheet out and their GP will be notified. GPs can open and discuss the fact sheet with their patient during the consult if they wish. Twenty-four hours after their consultation with the GP, HealthShare sends patients an SMS containing a link to the fact sheet. Final sample size will be determined by monthly reach of study advertising.

**EXPOSURES:** Control Period A – Advertisement is a clickable link and QR code with the words “Have your say about this fact sheet” in a red box in the top right corner of the fact sheet. Intervention Period B – Advertisement is a clickable link that mentions a financial incentive to participate: “Have your say about this fact

 Price et al (2022) Med Care. 2022 Dec; 60(12): 910–918.

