sheet. Complete a short survey **for your chance to win**” is written in a red box in the top right corner of the fact sheet. Intervention Period C – Advertisement is a clickable link with phrasing that appeals to social good: **“Help us improve fact sheets for people with back pain.”** Intervention Period D – Advertisement is a clickable link with phrasing that appeals to both social good and provides financial incentive: **“Help us improve fact sheets for people with back pain. Complete a short survey for your chance to win”** in a red box in the top right corner of the fact sheet.

COPYRIGHTED MATERIAL REDACTED

COPYRIGHTED MATERIAL REDACTED

Intervention period B

COPYRIGHTED MATERIAL REDACTED

COPYRIGHTED MATERIAL REDACTED

**Figure 4:** Three different advertising strategies to increase response rate to a fact sheet-based survey.

**OUTCOMES:** Proportion of people exposed to the survey advertisement who consent to participate

**SAMPLE SIZE:** A previous study comparing recruitment rates of different online recruitment methods suggest 27% response rate. To detect a difference in response rate of 5% (27% in control group, 32% in intervention group), with 80% power and 0.05 alpha, sample size required would be 1306 participants in each group (total n= 5224). The recruitment will stop at 5224 participants.

**ANALYSIS:** Descriptive analyses will be done to report the response rate for all participants according to trial period. We will compare the number and proportion of participants responding to messages.

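### The nested study's aim names BetterConsult, but one pooled response rate per period also counts GP-led sheets, so a change in route mix could not be told apart from a message effect

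*Supplement*

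**What the plan says.** All of this is in the Nested study section of the latest protocol version in the Supplement.

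- **Aim.** To assess survey advertising methods "using fact sheets embedded in consultation software (BetterConsult provided by the company HealthShare), on recruitment rate". The registry's stated reason for adding the nested analysis also names BetterConsult and no other tool.
- **Participants.** "Participants could receive a fact sheet via one of two methods". One is GP-led: "The first method is directly from their GP who prints and/or emails the sheet to their patient". The other is BetterConsult: "The second method is patient-led access to a back pain fact sheet via an SMS system called BetterConsult".
- **Design.** An ABACAD sequence in which the advertisement changes by period. A is the control wording; B, C and D are the alternatives.
- **Outcome.** "Proportion of people exposed to the survey advertisement who consent to participate", with no division by route.
- **Sample size.** 27% against 32%, 80% power, alpha 0.05, 1306 per group, 5224 in total.
- **Analysis.** "Descriptive analyses will be done to report the response rate for all participants according to trial period", followed by a comparison of the number and proportion responding to the messages. Route is not mentioned.

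**The concern.** The aim points to one delivery route and the population contains two, so it is unclear which response rate the study is meant to estimate.

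The routes differ in ways that could matter. Under Design, participants, and setting, the GP-led sheet comes from a sidebar in the consultation software and is passed on at the GP's discretion. The BetterConsult sheet is requested by the patient beforehand and arrives as an SMS link a day after the visit. The number of GP-led sheets in a period therefore depends on GP behaviour, which the study does not control.

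Because messages are compared across successive periods and not side by side, anything that differs between periods enters the contrast. Route mix is one such factor, and the plan as written would give the reader no means of seeing it.

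**Working it through.** **1. The plan's own figure.** Two proportions, 0.27 and 0.32, two-sided alpha 0.05, 80% power, pooled variance under the null:

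n = [1.96·√(2·0.295·0.705) + 0.8416·√(0.27·0.73 + 0.32·0.68)]² / 0.05² = 1305 per group.

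The plan states 1306, at which power is 80.0%, and 4 × 1306 = 5224. The sample size arithmetic is sound.

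**2. Inputs that the documents do not give.** The share of exposures that are GP-led (g), the GP-led response rate (r), and how strongly GP-led readers react to the wording. All three are assumed below. The SMS rate is set to the plan's 27%.

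**3. Mix shift with no message effect.** Pooled rate = 0.27(1 − g) + r·g. The false difference between two periods is (0.27 − r) × (change in g).

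| GP-led rate r | GP-led share, period 1 → 2 | Pooled rates | False difference |
|---|---|---|---|
| 20% | 30% → 20% | 24.9% → 25.6% | 0.7 points |
| 20% | 40% → 20% | 24.2% → 25.6% | 1.4 points |
| 10% | 30% → 20% | 21.9% → 23.6% | 1.7 points |
| 10% | 40% → 20% | 20.2% → 23.6% | 3.4 points |

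Against the 5-point target this is 14% (0.7/5) to 68% (3.4/5). In every row the difference within each route is zero, so a route-stratified difference is also zero. If r equals the SMS rate, or g is stable, the false difference vanishes.

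**4. Shrinkage if GP-led readers do not react to the wording.** The pooled effect is 5 × (1 − g) points. Power at 1306 per group depends on the GP-led base rate:

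| g | Pooled effect | Power, GP-led base 27% | Power, GP-led base 10% |
|---|---|---|---|
| 20% | 4.0 points | 61.5% | 64.9% |
| 30% | 3.5 points | 50.6% | 55.8% |
| 50% | 2.5 points | 29.4% | 36.1% |

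With half the effect in GP-led readers (base 27%), power is 71.5%, 66.7% and 56.1%. With the same 5-point effect in both routes the contrast does not shrink.

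**5. Would restricting to SMS alone recover power?** If the GP-led recipients are not replaced, 1306(1 − g) remain per group, and power is 70.8%, 65.0% and 50.8% at g = 20%, 30% and 50%. That beats pooling when GP-led readers show no effect, but not when they show half the effect.

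**6. Is route handled elsewhere?** The separate analysis by access method, under Design, participants, and setting, belongs to the main fact sheet comparison and is not carried into the nested study. The Fidelity question on how the sheet was received is answered only by people who enter the survey. It can classify consenters but gives no exposed denominator by route.

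**The case against.** **The aim may be meant more widely.** The GP sidebar also works within consultation software, and the Exposures section says both sheets are delivered through HealthShare's consultation tools. The bracketed BetterConsult may be loose wording, and the overall effect across both routes is a legitimate question. This stands. It makes the population something to reconcile; it does not show that GP-led sheets were included by mistake, and it does not supply a route split.

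**The repeated control periods help.** Steady drift in route mix would tend to show as differing rates in the three A periods. This stands in part. A change confined to one intervention period would leave no such trace.

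**Stronger readings that the documents do not support.** A reader might infer that GP-led recipients do dilute the message effect, or that a mix bias is present. Dilution needs a weaker reaction in GP-led readers; mix bias needs both unequal rates and shifting shares. None of these is documented. Nor is route the same as paper against screen: GP-led sheets may be emailed, SMS recipients may print theirs, and the message is a box on the sheet itself.

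A reader might also infer that printed sheets can be answered directly only in period A, since the text mentions a QR code for A and only a clickable link for B, C and D. The Procedure section puts a QR code on printed and emailed sheets, and the advertisement images are redacted, so this cannot be confirmed.

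**Restriction to SMS is not clearly better.** As step 5 shows, this is correct. It is a trade-off, not the default remedy.

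**Conclusion.** The point holds in a conditional form. The aim and the participants paragraph do not match, and the single pooled rate by period leaves a possible confounder unmeasured in a design without concurrent controls.

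Under the assumptions in step 3, the false difference runs from 0.7 to 3.4 points against a 5-point target; it could be nil. The power figures in step 4 only illustrate possible shrinkage. They rest on assumed shares and reactions, and the planned analysis is described as descriptive. The main fact sheet comparison is not affected. The change is worth making because it is cheap and would show whether the problem exists.

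**What to change.** 1. Reconcile the aim with the participants paragraph: state whether the nested question concerns BetterConsult only or both routes.
2. Use a route-specific survey link and QR code, and count exposed and consenting people by route and period.
3. Report response rates by route within each period. Base any overall message comparison on a route-stratified (Mantel-Haenszel) risk difference, not on the raw pooled proportion.
4. If exposed counts cannot be obtained for GP-led sheets, which the documents leave open for printed copies, limit the comparison to the BetterConsult SMS stream and restate the precision for the number reached.

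Cost: a few sentences in the nested protocol, some extra tracking and analysis work, and less precision within each route than in the pooled figure. If step 4 applies, either recruitment takes longer to reach 1306 per group or a smaller number has to be accepted.

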| Update                                                                                             | 
This study is quasi randomised. Participants are allocated to intervention and control groups via three methods. The first method is based on GP discretion as to which study fact sheet they provide to their patient. The comparison of outcomes for people allocated to fact sheet interventions via this method is therefore non-random. The second allocation method is random. Based on a computerised random number list, a GP software provider will allocate access to either the intervention or control fact sheet, for one month at a time for the duration of the trial. The comparison of outcomes for people allocated to interventions via this method is therefore based on a randomised computer generated sequence.
 
The third allocation method will be random. Participants via social media advertisement will be allocated to either intervention or control fact sheet randomly.
                                                                                                                                                                                                                                                                                                                                                                                         |

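### The nested study compares raw proportions by message across a fixed ABACAD sequence, so time drift biases the contrasts with control, most of all for D

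*Supplement*

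**What the plan says.** The protocol's Nested study section describes an "ABACAD replicated time series design". A is the control wording, B mentions a prize draw, C appeals to social good, and D does both. The aim is to "assess the effect of different survey advertising methods using fact sheets embedded in consultation software", and the outcome is "Proportion of people exposed to the survey advertisement who consent to participate".

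The sample size is set "To detect a difference in response rate of 5% (27% in control group, 32% in intervention group), with 80% power and 0.05 alpha", giving 1306 per group and 5224 in total.

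The Analysis paragraph has two sentences. The first is "Descriptive analyses will be done to report the response rate for all participants according to trial period". The second is "We will compare the number and proportion of participants responding to messages". The update to the statistical methods field of the registration record repeats both.

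Neither document gives a period length, a number of cycles, a randomised period order, a time term, or a control period after D.

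**The concern.** Control periods are placed between the message periods so that change over time can be separated from the effect of the wording. The stated comparison does not use them for that: it sets proportions side by side by message. If the response rate drifts for any other reason, part of the drift enters each contrast, and D is the most exposed because it comes after every A period.

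The documents give reasons to expect change over time. The survey may recruit for up to 12 months. According to the registration record, the software provider in the randomised GP-software route will "allocate access to either the intervention or control fact sheet, for one month at a time for the duration of the trial", so a change of fact sheet can coincide with a change of advertisement.

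At stake is the conclusion about which advertisement recruits best. The combined message could look better or worse than control for reasons unrelated to its wording.

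**Working it through.** **Inputs from the protocol:** 27% v 32%, 80% power, alpha 0.05, 1306 per group, 5224 in total, order ABACAD. **Assumptions:** two-sided test, equal periods (5224/6 = 871 exposures each) unless stated, linear drift of s points per period. The drift sizes and period SDs below are also assumptions, since the documents give none.

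**1. The plan's own figure.** For two independent proportions, with pooled variance under the null and mean proportion 0.295:

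n = [1.96·√(2·0.295·0.705) + 0.842·√(0.27·0.73 + 0.32·0.68)]² / 0.05² = 1305 per group.

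The stated 1306 reproduces, and 4 × 1306 = 5224. It is a calculation for independent groups with no allowance for time.

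**2. Drift bias.** A sits at positions 1, 3 and 5 (mean 3), B at 2, C at 4, D at 6. The bias of a raw contrast with pooled A is (position − 3) × s:

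- B: −1s
- C: +1s
- D: +3s

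A drift of 5/3 = 1.67 points per period would give D a spurious 5 points, the whole target difference. Running ABACAD twice leaves −1s, +1s and +3s unchanged in per-period units.

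Against adjacent A periods only, B (positions 1 and 3) and C (positions 3 and 5) have no bias from linear drift. D has only position 5 beside it and keeps +1s.

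**3. Type I error of D v A.** SE = √(0.295·0.705·(1/871 + 1/2612)) = 1.78 points. Two groups of 1306 give the same value. Type I error is P(|Z + bias/SE| > 1.96).

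| Drift per period | Bias of D | Bias/SE | Type I, D | Type I, B or C |
|---|---|---|---|---|
| 0.5 points | 1.5 points | 0.84 | 13% | 6% |
| 1 point | 3 points | 1.68 | 39% | 9% |

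**4. Cost of adjusting for a linear trend.** In a single cycle only the A periods identify the trend, so

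Var = 0.295·0.705·[1/n_message + 1/n_A + (position − mean A position)² / Σ n(t − mean A position)²], summing over A periods.

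For D with six equal periods: 1/871 + 1/2612 + 9/(871·8) = 0.00153 + 0.00129, a variance ratio of 1.84 and an SE of 2.42 points. Power is Φ(5/SE − 1.96). The two-cycle row comes from the same model fitted by weighted least squares.

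| Layout, 5224 exposures | Power B | Power C | Power D |
|---|---|---|---|
| ABACAD, six equal periods | 76% | 76% | 54% |
| ABACAD, 1306 per message, A split over three periods | 73% | 73% | 40% |
| ABACADA, seven equal periods (746 each) | 70% | 76% | 70% |
| ABACAD twice, twelve equal periods | 80% | 80% | 76% |

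**5. An added A period without a trend term.** In ABACADA the A periods have mean position 4, so the raw biases become −2s, 0 and +2s. The extra period does not replace the adjustment.

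**6. Random period-to-period variation.** With period SD τ and six periods, SE² = 1.78² + τ²(1 + 1/3). For τ = 1 point, SE = 2.13 and unadjusted power is 65%. For τ = 2 points, SE = 2.92 and power is 40%.

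**The case against.** The strongest reply is that the plan promises rates by trial period. The three A rates will therefore be visible, and B and C are each bracketed by controls. That stands as far as it goes. A reader might infer that any drift at all will pass unnoticed as an advertising effect, and the documents do not support that. But showing drift does not remove it from the message comparison, and no rule says what follows if it is seen.

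A second reply is that no analysis plan is shown, the first sentence calls the analysis descriptive, and no test is named. The type I figures do belong to a test the plan only implies. However, the aim is an effect, the study is sized with alpha and power, and the comparison that is stated gives a biased contrast under drift if followed as written. That is more than missing detail.

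A third is that "ABACAD replicated time series design" may mean the whole cycle is repeated. One might infer that B, C and D each run once, but the text does not settle this. With repetition an earlier D would be followed by A, and within a fixed calendar span the drift per period would be smaller. The final D would still have no control after it, and the biases in per-period units would stay the same.

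**Conclusion.** The point holds. Followed as written, the comparison is biased by −1s, +1s and +3s for B, C and D against pooled A, given equal periods and linear drift. At an assumed 0.5 or 1 point per period, D is biased by 1.5 or 3 points of a 5-point target, and a 5% test would have a type I error of about 13% or 39%. Unequal periods would change the multipliers, but within a cycle D still follows every A period.

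The stated 80% power covers neither the adjustment for time nor period-to-period variation. One might go further and require a period-level variance term in the model. That is not supported: six or seven periods leave too few degrees of freedom to estimate it (seven periods less intercept, three messages and trend leave two).

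The issue is confined to the nested recruitment study. It does not touch the primary PrepDM comparison.

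**What to change.** 1. Make the message comparison a logistic regression of consent on message with a calendar-time trend, adjusted for fact sheet and access channel where these are recorded for everyone exposed. Report each message's contrast with its adjacent A periods as the check.
2. Close the sequence with an A period or, if the sequence is repeated, state the number of cycles and period length, so that D is bracketed.
3. Restate the power for the layout chosen, using the table above, and say that period-to-period variation is not covered by it.

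The cost is a protocol amendment, some analysis work and a less favourable power statement. At 5224 exposures the stated 80% is not kept for every message. Moving from trend-adjusted ABACAD with six equal periods to ABACADA raises D from about 54% to 70% but lowers B from about 76% to 70%, with 746 exposures per message period. Two full cycles do best (about 80%, 80% and 76%) but need more changes of advertisement. The trend is assumed linear, and the adjacent-period contrasts are a partial check on that. If the sequence can no longer be changed, the first and third items can still be done.

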**ETHICAL ISSUES:**

*Consent*

We are seeking a waiver of consent for participants of the nested study (ie people exposed to the advertisement) because it is impractical and because obtaining consent would create a greater burden to participants than the interventions themselves.

*Monetary incentives*

Fair distribution of benefits and risks of research is one of the key principles of ethical research. Participants invest their time to participate in research deserve

some benefit in return. We will provide this in the form of a ticket to a lucky draw to win one of 5 Myer vouchers valued at \$100.

It is appropriate to provide such incentive to participants in research projects that are not risk rated as high risk, such as this project. We will maintain the anonymity of responses, while having a mechanism to send participants the incentive and enter them into the draw at the same time. For this we will separate the data collection and the incentive mechanism by entering the data from the completed instrument and the incentive entry in completely separate tables without any relational link between the two tables.

In running the lucky draw, we will comply with the NSW lottery laws and draws will be administered and conducted by someone independent of the research team. We are using the same approach in another HREC approved project (ID 2023/ETH00472 – Southwest Sydney Local Health District HREC)

## Exposures

Exposures will be two recently published, evidence-based resources for low back pain. The *JAMA Patient Page* (Available from: <https://jamanetwork.com/journals/jama/fullarticle/2782184>) was published on 20/7/21 and describes guideline-

endorsed medical and non-medical management options for low back pain.

The *Australian Commission for Healthcare Safety and Quality (ACHSQ) Information for Patients Fact Sheet* (Available from: <https://www.safetyandquality.gov.au/publications-and-resources/resource-library/how-manage-your-low-back-pain-information-patients>) was published on 22/9/22 and describes how to self-manage low back pain.

Both factsheets have been implemented into routine practice via HealthShare consultation tools.

## Statistical analysis

Our primary analysis will compare the PrepDM scores in people exposed to the JAMA fact sheet vs the ACHSQ fact sheet, immediately after they have read the sheet. Assuming a mean difference of 6 points on a 100-point scale (ie 60 points in JAMA fact sheet group, 54 points in ACHSQ group, SD of 26) with 90% power, we require a sample size of 790. To account for anticipated uneven group size we will increase the minimum sample size to 1000.

For the secondary outcomes of management intentions, reassurance, and acceptability, we compare means and proportions where applicable in the whole sample and generate 95% confidence intervals.

---

 Western Sydney University. Human Research Ethics. Guidance on Reimbursements. 2020.

 Dhand, N. K., & Khatkar, M. S. (2014). Statulator: An online statistical calculator. Sample Size Calculator for Comparing Two Independent Means. Accessed 8 May 2023 at <http://statulator.com/SampleSize/ss2M.html>

